**Figure 1 F1:**
[figure not shown]
Flow of participants through the study. NHS, National Health Service; QoL, quality of life.

### Strengths and needs assessment (assessment group only at T1)

The strengths and needs assessment includes 265 items in three areas: (1) body structure and function: what a person is able to do and what they are like as a person (eg, perception, temperament, memory, intellectual ability); (2) activities and participation: what a person does or does not do, taking into account different contexts (eg, how a person uses knowledge in order to solve problems, to what extent they take care of their health) and (3) environmental factors: aspects of a person’s environment that can either facilitate or hinder everyday functioning (eg, family relationships, social norms). These items ask about day-to-day functioning within the last month.

Questions are answered on a 0–10 scale (eg, 0–5=‘Do not’, 6–8=‘Do’, 9–10=‘Do to a great extent’) with the option to add comments to each answer. Lower scores represent areas of need, while higher scores represent strengths. The questionnaire is hosted on an online platform, and participants can complete the assessment across as many sessions as they wish using a computer, phone or tablet. Piloting in the UK and Sweden suggests that completion time is highly variable but averages between 30–60 min.^28 31^ After completing the assessment, participants will be emailed their summary report which describes areas of strength and need. This will be accompanied by a debrief form with signposting to support and resources.

### Primary outcome measures

The primary study outcomes are the acceptability and usability of the strengths and needs assessment, and the acceptability and feasibility of the trial procedures. Acceptability of the strengths and needs assessment will be measured using a single item from the TFA^30^: ‘How acceptable was the assessment to you?’. This is answered on a 5-point Likert scale from completely unacceptable to completely acceptable. The SUS^29^ will assess the usability of the assessment. This is a 10-item questionnaire answered on a 5-point Likert scale. Responses are summed and scaled to give an overall usability score which can be used to categorise interventions (eg, poor, ok, good, excellent). The SUS has demonstrated reliability and concurrent validity with measures of perceived and objective usability.^37^

Completion times for the strengths and needs assessment and outcome measures will be recorded and reported using sample medians. For those who drop out, time on task until drop-out will be recorded and reported.

The acceptability and feasibility of the trial procedures will be measured by collecting procedural data from the participating sites (eg, the number of participating clinicians, clinician time required to distribute participant invitations, service user eligibility rates). The study team at the University of Sheffield will collect data on recruitment rates and representativeness, adherence rates for the outcome measures and the attrition rate in each arm of the study. Participant interviews and clinician focus groups will also be used to evaluate the acceptability and feasibility of study procedures, barriers and facilitators to study participation, perceived value in the strengths and needs assessment, and any adverse events associated with the study.

### Secondary outcome measures

The secondary outcomes are the demographics (age, gender, ethnicity) and current mental health status of the autistic adults recruited into the sample. This will be used to show the representativeness of the sample and levels of well-being in the sample. It will also give some preliminary data around whether the strengths and needs assessment has an impact on well-being levels and whether it would be feasible to measure mental health outcomes in this way in a larger trial.

Mental health/QoL outcomes will be measured using the following:

The 5-level EQ-5D^38^ is National Institute for Health and Care Excellence’s preferred measure of health-related QoL in adults^39^ and is necessary for health economic evaluation to assess quality-adjusted life-years.The Patient Health Questionnaire-9^40^ (PHQ-9) measures levels of depression, self-harm and suicide risk. The PHQ-9 has good sensitivity and specificity for detecting depressive disorders.^41^ This outcome measure will be used to monitor for adverse events during the study. If participants score in the severe range (20–25) on the PHQ-9, this will trigger a letter to be sent to their GP.The Generalised Anxiety Disorder-7 (GAD-7)^42^ measures levels of anxiety. The GAD-7 has good sensitivity and specificity for detecting generalised anxiety, panic, social anxiety and post-traumatic stress disorders.ReQoL-10^43^ is an important measure to support future health economic evaluation. This estimates utilities and hence QALYs and is now part of the core value set for mental health conditions.

These mental health and QoL measures will be collected at T1 and T2 (3-month follow-up). The questionnaires will be hosted online using Qualtrics^44^ and participants will be emailed links to access them. A previous trial^31^ suggests that these questionnaires will take between 10 and 20 min to complete at each timepoint.

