The study will also evaluate the acceptability and feasibility of the trial design in preparation for a future definitive randomised control trial (RCT). The UK’s Medical Research Council’s framework for evaluating complex interventions^34^ highlights the importance of piloting prior to larger efficacy trials being carried out. This identifies potential problems which could lead to underpowering in larger trials and provides estimates for trial sample sizes. Acceptability will be evaluated in interviews with participants and focus groups with clinicians. The feasibility of the proposed recruitment, randomisation and data collection methods will be evaluated against a list of progression criteria before planning for a future trial.

Specifically, the research questions are

RQ1a: Are the proposed recruitment, randomisation and data collection methods acceptable and feasible for use within NHS adult autism diagnostic services?

RQ1b: Is the ICF CoreSets for Autism Strengths and Needs Assessment acceptable for use by autistic adults on receipt of an autism diagnosis?

RQ1c: What are the potential benefits or harms of completion of the ICF CoreSets for Autism Strengths and Needs Assessment?

The secondary aim is to gain a thorough understanding of the characteristics and mental health status of the populations receiving autism diagnoses in these clinical settings. We will use mental health and quality of life (QoL) outcome measures to answer the secondary research question:

RQ2: What are the demographics and current mental health status of adults being diagnosed in NHS services?

Mental health measures will also be used to monitor for adverse events arising from study participation. They will also provide preliminary data on whether the strengths and needs assessment improves well-being outcomes and how feasible it is to use these measures to measure efficacy in a larger trial.

The study will be reported according to Consolidated Standards of Reporting Trials guidelines for reporting randomised pilot and feasibility trials.^35^ If effective, the ICF CoreSets for Autism Strengths and Needs Assessment have the potential to be implemented in NHS diagnostic services as a standardised approach to providing post-diagnostic support for autistic adults.

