Both groups will complete online QoL and mental health questionnaires at baseline (T1) and at 3 months follow-up (T2). Only the assessment group will be asked to complete the strengths and needs assessment. A link to complete the strengths and needs assessment will be emailed immediately after baseline measures are completed. Participants will be told that they can email the researcher with any questions about the assessment or to provide support during the completion process. They will also be told that they can do the assessment in as many sittings as they choose to (responses are saved on the platform continually) and that they can complete the assessment over a 2-week period.

Participants will receive voucher payments of £20 for completing their T1 measures and £10 for completing T2 measures. Participants who do not complete measures will receive a reminder email with contacts for the research team at the University of Sheffield and links to support services.

A subsample of 12 participants (four from each service: two from the Assessment group and two from the treatment as usual group) will also be invited to take part in an interview after T2. They will be provided with additional information for these interviews and will be asked to consent to take part. The interviews will be held mainly online, although some will be hosted in the diagnostic services, if participants prefer, and services have capacity to offer this. The interviews will follow a semi-structured schedule which will cover the acceptability and feasibility of the study procedures and the strengths and needs assessment, any barriers or facilitators to trial participation, any adverse effects of participation and their personal experiences of post-diagnostic support. Interviews will last for around 30 min and will be recorded and transcribed verbatim. Participants will receive voucher payments of £20 for taking part in an interview. Participating clinicians and administrators (involved with the set up or running of the study at each site) will be invited to take part in a focus group at each diagnostic service following the 6-month data collection period. Figure 1 shows the movement of participants through the study.

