### Ethics and dissemination

Participants will receive information about the study via an information leaflet which includes links to further information about the study and the contact details of the research team. Participants will give informed consent before participating in the study. The study team will signpost to appropriate resources and support during the study and will monitor and flag adverse events (eg, severe mental health difficulties) resulting from study participation. Participants are able to withdraw from the study by informing the research team at the University of Sheffield. This will not impact the care they receive from their diagnostic setting.

The study protocol was reviewed by East Midlands—Nottingham 2 Research Ethics Committee and given ethical approval on 18 March 2025. The study has been registered on ISRCTN (ISRCTN10283350) and has been adopted onto the NIHR study portfolio (CPMS: 66984). Any protocol modifications will be submitted by amendment via the NIHR’s IRAS procedure.

The results of the study will be disseminated via reports to the funder (NIHR), a peer-reviewed journal paper and academic conferences. We will email a summary report of findings to study participants and will invite study participants to an information dissemination event at the end of the study. Links to reports and a lay summary will be provided on the research group’s website: https://sharl.sites.sheffield.ac.uk/home Anonymised study data will be deposited in the University of Sheffield’s data repository at the end of the study (eg, outcome scores on mental health measures, coding frames for qualitative data). This will not include responses to the strengths and needs assessment, demographic data or interview transcripts.

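### The PHQ-9 severe-range rule works as a care alert, but it cannot identify adverse events arising from participation, and no stated analysis counts individuals who deteriorate in each arm

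*Protocol article*

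**What the plan says.** All references are to the protocol article.

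- **Harms question (Introduction).** Among the research questions is "RQ1c: What are the potential benefits or harms of completion of the ICF CoreSets for Autism Strengths and Needs Assessment".
- **Monitoring aim (Introduction; Ethics and dissemination).** "Mental health measures will also be used to monitor for adverse events arising from study participation". The ethics section says the study team "will monitor and flag adverse events (eg, severe mental health difficulties) resulting from study participation".
- **Instrument and rule (Secondary outcome measures).** Of the PHQ-9: "This outcome measure will be used to monitor for adverse events during the study". The next sentence reads: "If participants score in the severe range (20–25) on the PHQ-9, this will trigger a letter to be sent to their GP". The rule is not limited to one time point and does not refer to an earlier score. No individual-level rule is given for the GAD-7.
- **Timing (Secondary outcome measures; Study procedures).** The measures are taken at T1 (baseline) and T2 (3 months). "A link to complete the strengths and needs assessment will be emailed immediately after baseline measures are completed".
- **Other evidence on harm.** Data analysis plans a between-arm model of change from T1 to T2 in PHQ-9, GAD-7, EQ-5D-5L and ReQoL-10. Study procedures plans 12 interviews, which also ask about adverse effects. Primary outcome measures lists adverse events among the topics of the interviews and clinician focus groups.

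**The concern.** The article names a purpose (detecting events caused by taking part), an instrument (the PHQ-9) and a threshold (an absolute level). The threshold does not fit the purpose. A level says how unwell someone is on the day. It does not say whether they have become worse since joining, and still less whether the assessment had a part in it.

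What is at stake is how well the pilot can answer RQ1c and inform safety planning for a definitive trial. Such a trial needs to know how many people deteriorate after completing a long assessment just after diagnosis, compared with how many do so under usual care. A mean can stay flat or improve while a few people get clearly worse, so an analysis of average change does not supply that number.

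**Working it through.** The article states no PHQ-9 mean, SD, severe rate or test-retest correlation, so there is no figure of its own to reproduce. The check is first one of logic, then an illustration under stated assumptions.

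**1. Sequence.** T1 measures are completed, then the assessment link is sent. A severe score at T1 therefore cannot be an effect of completing the assessment. A severe score at T2 may be new or may have been there at T1, and the rule treats the two alike.

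**2. Worsening below the range.** A move from 5 at T1 to 19 at T2 is a rise of 19 − 5 = 14 points and triggers nothing.

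**3. Triggers before exposure.** With an assumed 10% to 30% of participants severe at T1: 72 × 0.10 = 7.2 and 72 × 0.30 = 21.6, so about 7 to 22 people. These are GP-letter triggers, not a planned adverse event count.

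**4. Level versus change.** 400,000 T1/T2 pairs were simulated with no true effect for each combination of mean 10, 13 or 16, SD 5 or 6.5, and T1–T2 correlation 0.5, 0.7 or 0.8. Scores were rounded and bounded at 0 to 27. A score of 20 or more counted as flagged, and a rise of 5 or more as worsening. All of these inputs are assumptions, and the 5 points are for illustration only.

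| Mean, SD, correlation | Flagged at T1, of 36 | T2 flags already severe at T1 | T2 flags without a rise of 5 or more | Rises of 5 or more not flagged at T2 |
|---|---|---|---|---|
| 10, 5, 0.5 | 1.0 | 19% | 38% | 90% |
| 13, 5, 0.7 | 3.5 | 46% | 69% | 76% |
| 16, 6.5, 0.8 | 10.6 | 70% | 80% | 54% |
| Range over all 18 settings | 1.0 to 10.6 | 19% to 70% | 38% to 86% | 47% to 91% |

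The percentages move a good deal with the assumptions. In every setting, though, the level both mixes in existing severity and misses a large part of the worsening.

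**5. What the other sources can show.**

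- *Model of change.* It gives average change by arm and is presented as an analysis of effectiveness. Its stated effect size, partial eta-squared, has no sign; the reported means will show direction, but not how many people worsened.
- *Interviews.* Three services × two = 6 assessment-group participants. The chance that at least one of them has a harm with true rate p is 1 − (1 − p)^6: 26% at p = 5%, 47% at 10%, 74% at 20%.
- *Focus groups.* Clinicians are not to be told who takes part or in which arm. If that holds (the article doubts that it fully will), they can hardly attribute events to an arm.

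**The case against.** The strongest reply is that the GP letter is a care action and not an outcome definition. A reader might infer that severe-range scores will be counted as adverse events, so that the count would mostly reflect baseline severity. The article does not say this: it ties the score to a letter and plans no such count. That part of the reply stands.

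A reader might also infer that the harms question goes unanswered, or that the PHQ-9 cut-off is the only quantitative signal. Neither is supported. The randomised comparison of change uses T1 scores, covers four measures and can point in either direction. Attrition is recorded by arm, and adverse effects are asked about in interviews. Nor is it true that the data could yield no harm rate by arm: T1 and T2 scores are planned for everyone, so individual worsening can be derived later.

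It can further be said that adverse event definitions and tables often sit in a full protocol or analysis plan, which is not shown. This limits the point but does not remove it. The article itself gives the PHQ-9 the monitoring task and states one rule, and that rule does not match the task.

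Finally, with at most 36 per arm any count will be imprecise: 4 of 36 has an exact 95% CI of about 3% to 26%. That is so, and it is a reason to report the count descriptively, not to omit it.

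**Conclusion.** The point holds in a limited form. The severe-range rule is usable as a care alert. It is not a measure of events arising from participation, because it applies before the assessment is sent and takes no account of change. RQ1c is partly addressed by other planned work, but nothing stated gives the number of individuals who deteriorate in each arm.

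The mismatch between rule and purpose follows from the text alone. Its numerical size cannot be fixed from the article: the 7 to 22 letter triggers and the simulated ranges rest on assumed distributions. The point is moderate to minor. It does not threaten the trial's design and can be settled with data already planned, but it concerns a named research question and should be settled before the T2 data are seen. No view is taken on the clinical threshold or on the letter.

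**What to change.** Leave the GP-letter rule as it stands and say that it is separate from the harms outcome. Then state for RQ1c:

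1. Severe-range PHQ-9 scores at T1 are reported as baseline status.
2. Reported descriptively by arm, with 95% CIs: (a) the number not in the article's severe range at T1 who are in it at T2; (b) the number who worsen from T1 to T2 on the PHQ-9, and likewise on the GAD-7, by an amount the team fixes before seeing the data.

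The denominators should be given, with the number lacking a T2 score in each arm, since people who deteriorate may be among those lost.

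The cost is a sentence or two in the plan and two extra table rows; no new data are needed. There are two limits. The intervals will be wide: even zero events in 36 leaves a one-sided 95% upper bound of 1 − 0.05^(1/36) = 8.0%. Scores also fluctuate: in the simulation without any effect, 8% to 24% rose by 5 or more points, which is 36 × 0.08 = 2.9 to 36 × 0.24 = 8.6 people per arm. The counts should therefore be read against the usual-care arm and not as harm rates on their own.

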### Participants

The trial will recruit 72 autistic adults who have received a diagnosis of autism from one of the three participating clinical services (24 in each service). Participants will be adults (18+years) and will not have a diagnosis of a co-occurring learning disability. Clinicians will not invite individuals with a diagnosed intellectual disability to take part in the study. Participants will be recruited over a 6-month period from 1 April 2025 until 1 October 2025 or until the service target sample (24) has been recruited. The sample size is in line with guidance recommending a sample size of 70 for a two-arm randomised pilot study.^30^

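### The PHQ-9 range that triggers a GP letter stops at 25, so as printed the highest scores trigger no letter

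*Protocol article*

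**What the plan says.** The rule is in the protocol article, Methods and analysis, Secondary outcome measures, in the description of the PHQ-9: "If participants score in the severe range (20–25) on the PHQ-9, this will trigger a letter to be sent to their GP". The sentence before it gives the measure its safety role: "This outcome measure will be used to monitor for adverse events during the study". The Introduction says the same of the mental health measures in general: "Mental health measures will also be used to monitor for adverse events arising from study participation". The questionnaires are completed online at baseline (T1) and at 3 months (T2).

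Under Ethics and dissemination, the study team "will monitor and flag adverse events (eg, severe mental health difficulties) resulting from study participation", with no score attached. The article gives no other PHQ-9 cut-off, no item scoring, no scale maximum, and no rule for totals above 25.

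**The concern.** The words and the numbers in the trigger disagree. A severe range should contain the most severe scores, but the printed range is closed at 25, and the PHQ-9 total can go higher. Someone applying the label would send a letter for every total from 20 up. Someone applying the printed numbers, for example in a filter on exported online scores or a monitoring checklist, would send none for the highest totals, and nothing would show that they had been missed.

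The GP letter matters more than usual in this design. The measures are completed remotely. Under Study procedures and Reliability and validity, the diagnosing clinicians are deliberately not told who takes part. The letter is therefore the only route stated in the article by which a severe score reaches a treating clinician. The article also describes the PHQ-9 as covering self-harm and suicide risk.

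**Working it through.** **Inputs**

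- Printed trigger: totals 20 to 25 (Secondary outcome measures).
- Number of items: nine, taken from the name PHQ-9; the article does not state it separately.
- Item scoring: not stated. Items are assumed to be scored alike, in whole numbers from 0 to k. The usual scoring is k = 3; other values are shown as a range.
- Planned sample 72 (Participants); two time points, T1 and T2 (Secondary outcome measures).

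**Step 1. Can 25 be the top of the scale?** The maximum total is 9 × k. A maximum of 25 would need k = 25/9 = 2.78, which is not a whole number. The printed upper limit cannot be reproduced as the scale maximum.

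**Step 2. Which totals does the printed range leave out?**

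| Item scoring | Maximum (9 × k) | Totals from 20 up | Of these, above 25 |
|---|---|---|---|
| 0–1 | 9 | none | none |
| 0–2 | 18 | none | none |
| 0–3 | 27 | 20–27: 8 values | 26, 27: 2 values |
| 0–4 | 36 | 20–36: 17 values | 26–36: 11 values |
| 0–5 | 45 | 20–45: 26 values | 26–45: 20 values |

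For k = 1 or 2 the trigger could never be reached, so k must be at least 3. Every scale with k of at least 3 has totals above 25. That a gap exists therefore needs only nine equally scored whole-number items and the printed lower limit of 20. Naming the gap as 26 and 27 needs k = 3.

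**Step 3. What do the omitted totals mean for a single item (k = 3)?** Any eight items sum to at most 8 × 3 = 24, so with a total T the remaining item scores at least T − 24.

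- T = 20: 20 − 24 is negative, so any one item can be 0.
- T = 26: every item is at least 26 − 24 = 2.
- T = 27: every item is 27 − 24 = 3.

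At 26 and 27, any item on self-harm must therefore score 2 or 3. At 20 it may be 0. Read literally, the rule covers the second case and drops the first.

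**Step 4. How often does the rule apply?** At most 72 × 2 = 144 scheduled PHQ-9 completions. This counts forms, not people at risk. The article gives no score distribution, so the number of totals at 26 or 27 cannot be estimated.

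**The case against.** The strongest reply is that the operative condition is the label. The letter follows a score in the severe range, and the bracketed numbers only explain that term. A total of 26 is more severe, not outside severe, and a sensible monitor would act on it. On this view the range is a misprint and nothing shows that it was programmed as printed. That is a fair account of what was probably intended, but it does not make the printed numbers right, and it gives no assurance about the rule in use.

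Second, the article states neither the item count nor the scoring, so the point rests partly on assumptions. This is true for naming 26 and 27. It is much weaker for the gap itself, which appears under every equal whole-number scoring that can reach 20. The article does not say that 25 is the scale maximum, so it might be the top of one band. In that case the totals above it would have no stated rule at all, and the gap would remain.

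Third, other safeguards have no ceiling: the general undertaking to flag severe mental health difficulties, signposting to support, debrief forms, and adverse events raised in interviews and focus groups. A total of 26 would not escape all handling. But the undertaking gives no cut-off, and signposting and debrief forms go to the participant, not to a treating clinician.

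Fourth, a journal article condenses the full protocol, where the escalation procedure may be correct. This limits the conclusion to the figure as printed. The error is a stated figure, not an omitted detail, so it still needs correcting.

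**Conclusion.** The printed trigger is wrong as written: its upper limit of 25 falls short of the top of the scale, and no other rule in the article covers the totals above it. Under 0–3 scoring, 2 of the 8 totals from 20 upward, the two highest, are uncovered.

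The conclusion assumes nine items scored alike in whole numbers from 0; the specific totals 26 and 27 also assume 0–3 scoring. It does not claim that any letter was withheld. The cause is probably a misprint, the number of participants affected may be zero, and the planned analyses and the sample size of 72 are untouched. It should be fixed because it is a wrong threshold in the only numeric participant-protection rule the article states.

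**What to change.** Replace the range with a PHQ-9 total of 20 or above (20–27). Check the rule actually applied at T1 and T2, in the scoring file or monitoring checklist, and confirm that it has no upper limit of 25. If it did stop at 25, identify anyone who scored above it and send the letter.

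This last step is time-limited, because Data management says all personal data will be deleted after the study. The corrected figure should also be carried into the planning of the definitive trial.

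The cost is one corrected figure and one check of the rule in use. No new data are needed and no analysis changes.

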### Data management

Data will be managed by the research team at the University of Sheffield following a DPIA with Sheffield Health Partnership University NHS Foundation Trust. Personal data will be stored separately from study data and will be used only to contact participants for the purposes of the research. All data will be anonymised before reporting and storing. After the study, all personal data will be deleted.

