### Trial status

Recruitment of participants to the study will start from 7 April 2025. It is expected that recruitment will finish by 1 October 2025 and that data collection will be finished by the end of January 2026.

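### The PHQ-9 trigger for a GP letter is printed as a closed band, 20–25, which read literally leaves out the highest scorers

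*Protocol article*

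**What the plan says.** Under Secondary outcome measures, the protocol article gives the PHQ-9 a safety role as well as an outcome role: "This outcome measure will be used to monitor for adverse events during the study". The action attached to it is: "If participants score in the severe range (20–25) on the PHQ-9, this will trigger a letter to be sent to their GP". The scores arise at two timepoints: "These mental health and QoL measures will be collected at T1 and T2 (3-month follow-up").

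Two other places bear on safety, and neither gives a score. The Introduction says: "Mental health measures will also be used to monitor for adverse events arising from study participation". Ethics and dissemination says that the study team "will monitor and flag adverse events (eg, severe mental health difficulties) resulting from study participation".

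The article prints neither the PHQ-9 item scoring nor its maximum total, and it sets no separate action for totals above 25.

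**The concern.** A trigger for the severe end of a scale should have no upper limit, or should stop at the scale's maximum. This one stops at 25. If the scale goes higher, the rule as printed sends a letter for a total of 25 and none for a total of 26, which reverses its purpose.

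What is at stake is participant safety. By the article's own description, the PHQ-9 covers self-harm and suicide risk as well as depression. The questionnaires are completed online, and the diagnosing clinicians are not told who has joined the study. The research team's check of the score is therefore the main route the article describes from a high total to a clinician. The article contains no other numeric safety threshold.

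There is also a time limit. Data management states: "After the study, all personal data will be deleted". Trial status expects that "data collection will be finished by the end of January 2026". Once identities are gone, a participant who was missed can no longer be followed up.

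**Working it through.** **Inputs**

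- Trigger band: 20 to 25 inclusive (Secondary outcome measures).
- Number of items: 9, taken from the name of the instrument, "The Patient Health Questionnaire-9". The article does not state the item count separately.
- Timepoints: 2, T1 and T2 (Secondary outcome measures).
- Planned sample: 72 (Participants).
- Assumption, because the article does not print the scoring: all nine items have the same whole-number maximum k and are summed without weights.

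**Step 1: can 25 be reproduced as the top of the scale?**

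The highest possible total is 9 × k. Setting 9k = 25 gives k = 25/9 = 2.78, which is not a whole number. From the other side, a top of 25 would need 25/3 = 8.33 items with a maximum of 3, or 25/4 = 6.25 items with a maximum of 4. The printed limit is not reproduced. Whether items start at 0 or at 1 makes no difference, because the highest total is 9k either way.

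**Step 2: which totals fall outside the band?**

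| Item maximum k | Highest total 9k | Possible totals from 20 upward | Covered (20–25) | Not covered |
|---|---|---|---|---|
| 1 | 9 | none | – | band unreachable |
| 2 | 18 | none | – | band unreachable |
| 3 | 27 | 27 − 20 + 1 = 8 | 6 | 2 (26 and 27) |
| 4 | 36 | 36 − 20 + 1 = 17 | 6 | 11 (26 to 36) |

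The rows k = 1 and k = 2 are ruled out, because the trigger could then never fire. The smallest workable case, k = 3, already leaves 26 and 27 uncovered, and a larger k leaves more. The row k = 4 only shows the direction; nothing in the article points to it.

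**Step 3: is the gap closed elsewhere?**

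No. The statements in the Introduction and in Ethics and dissemination promise monitoring and flagging, but attach no score and no GP letter.

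**Step 4: upper bound on a re-screen**

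72 participants × 2 timepoints = 144 PHQ-9 totals at most, and fewer after any loss to follow-up.

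The counts in step 2 are possible scores, not people. The article gives no PHQ-9 distribution, so the expected number of participants above 25 cannot be calculated from it.

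**The case against.** The strongest reply is that this is a slip of the pen. The operative words are the severe range, and the figures in brackets only gloss them. Staff who apply the severe category would send a letter at 26 or 27 without hesitation. The article condenses a protocol that an ethics committee reviewed, and the working safety procedure may well be correct there. High scorers also have other cover: the commitment to flag severe mental health difficulties has no threshold and therefore no cap, and the debrief material signposts to support. Finally, the arithmetic relies on a scoring rule that the article does not print.

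Much of this stands. A misprint is the most likely explanation, no document shows that a cap was ever applied, and the number of people affected would probably be small. It does not remove the point. If the figure is a misprint, it is a misprint in a safety threshold and still needs correcting. General flagging and signposting do not replace a GP letter. The scoring assumption is mild: any equal whole-number scoring of nine summed items that can reach 20 leads to the same conclusion. Nothing in the article suggests that 25 was a deliberate limit, since no higher band and no other action is described.

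**Conclusion.** The point holds. As printed, the GP-letter trigger has an upper limit that cannot be the top of the scale, and it leaves out at least the totals 26 and 27. With an item maximum of 3, that is 2 of the 8 possible totals from 20 upward. This rests on nine equally scored items summed without weights; the exact ceiling of 27 rests further on the item maximum of 3.

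The consequence is confined to participant safety. The primary outcomes, the sample size and the planned analyses are untouched. Whether anyone was missed depends on whether the procedure in use carries the cap, which the article does not show. Correction is warranted because the omission falls on the most severe scorers and costs almost nothing to remove. The lower threshold of 20 is not in question.

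**What to change.** 1. State the trigger as a PHQ-9 total of 20 or above, with no upper limit.
2. Check the GP-letter procedure, and any automatic alert in the online questionnaire if there is one, to confirm that neither stops at 25.
3. Only if a cap is found, look up the T1 and T2 totals collected so far, send any letters that were missed, and do this before personal data are deleted.
4. Carry the corrected rule into the procedures for the definitive trial.

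The cost is one corrected figure and one check of the procedure. In the worst case it adds a look-up of at most 144 totals.
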